### Statistical Analysis

The primary analysis will be according to the intention-to-treat principle and complemented with a per protocol analysis.^41^ Nonadherence refers to patients who fail to receive the intervention or placebo after randomization, owing to cancelled operation or refusing to participate on the day of surgery. To control bias from nonadherence, sensitivity analyses will be conducted excluding participants with nonadherence.

### Baseline Analyses

To compare baseline characteristics, continuous variables will be given as mean (SD) for normal distribution or median (interquartile range) for skewed distribution. Categorical variables will be given as numbers (percentages). Clinical characteristics will be compared between the intervention and control groups using the unpaired 2-tailed *t* test or the Mann-Whitney test for continuous variables and with the use of the χ^2^ test or Fisher exact test for categorical variables.

### Primary Outcome Analysis

The primary outcome of our analysis is the incidence of emergence delirium. Comparisons in delirium incidence between the 2 groups will be assessed with a χ^2^ test, and 95% CIs will be calculated for the difference in delirium incidence.

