### Intervention and Study Visits

#### Baseline Hospital Ward Visit

Baseline assessments are conducted in the hospital ward. Demographic information, medical history, health history (eg, long-term alcohol use and smoking status), hearing and vision measurement, baseline laboratory tests, and electrocardiography are collected from the electronic medical record. One day before surgery, patients undergo assessments, including pain measured by a visual analog scale,^28,29^ depression by the 9-item Patient Health Questionnaire,^30^ anxiety by the 7-item Generalized Anxiety Disorder Scale,^31^ insomnia by Insomnia Severity Index,^32^ and cognitive function by the Montreal Cognitive Assessment,^33^ with the aim of identifying risk factors of emergence delirium. All planned study visits are presented in the Table.

**Table. zoi200508t1:** The Schedule of Planned Investigation

Study component	Visit 1	Visit 2	Visit 3	Visit 4	Visit 5	Visit 6	Visit 7	Visit 8
Time	1 d before surgery	Before anesthesia	During anesthesia	PACU	POD 1	POD 2	POD 3	Hospital discharge
Eligibility screen	X	−	−	−	−	−	−	−
Informed consent	X	−	−	−	−	−	−	−
Demographic characteristics	X	−	−	−	−	−	−	−
Randomization	X	−	−	−	−	−	−	−
Intervention	−	X	−	−	−	−	−	−
MoCA	X	−	−	−	−	−	−	−
VAS	X	−	−	X	X	X	X	−
PHQ-9	X	−	−	−	−	−	X	−
GAD-7	X	−	−	−	−	−	X	−
ISI	X	−	−	−	−	−	X	−
EEG frequency spectrum	−	X	X	X	−	−	−	−
Blood draw for biomarkers	−	X	−	X	−	−	−	−
CAM-ICU	−	−	−	X	X	X	X	−
Nausea and vomiting	−	−	−	X	X	X	X	−
Adverse events	−	−	−	X	X	X	X	−
Hospital stay	−	−	−	−	−	−	−	X

Abbreviations: CAM-ICU, Confusion Assessment Method for the Intensive Care Unit; EEG, electroencephalography; GAD-7, 7-item Generalized Anxiety Disorder Scale; ISI, Insomnia Severity Index; MoCA, the Montreal Cognitive Assessment; PHQ-9, 9-item Patient Health Questionnaire; POD, postoperative day; VAS, visual analog scale; X, present; minus sign, absent.

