### Priori Subgroup Analyses

Known confounders have an impact on delirium; thus, subgroup analyses will be conducted by comparisons of prespecified subgroups for the primary outcome. These include age (>65 years vs ≤65 years), surgery type (major vs minor), and preoperative Montreal Cognitive Assessment scores (>26 vs 18-26 vs 10-17) to eliminate the impact of these factors on tropisetron efficacy.

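### The unadjusted primary chi-square is valid but gives up a modest amount of precision, and the planned subgroups cannot remove the influence of age, surgery type and MoCA from the overall estimate

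*Protocol article*

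**What the plan says.** Under Primary Outcome Analysis, the protocol article states: "Comparisons in delirium incidence between the 2 groups will be assessed with a" chi-square "test, and 95% CIs will be calculated for the difference in delirium incidence". No covariate is named.

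The next section, Priori Subgroup Analyses, begins: "Known confounders have an impact on delirium; thus, subgroup analyses will be conducted by comparisons of prespecified subgroups for the primary outcome". It continues: "These include age (>65 years vs ≤65 years), surgery type (major vs minor), and preoperative Montreal Cognitive Assessment scores", the last in three bands. The purpose given is "to eliminate the impact of these factors on tropisetron efficacy". Strengths and Limitations repeats the idea that subgroup analyses will mitigate confounding.

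All three factors are recorded. Demographics come from the electronic record at the Baseline Hospital Ward Visit. Patients are assessed one day before surgery, including pain, mood, sleep "and cognitive function by the Montreal Cognitive Assessment", "with the aim of identifying risk factors of emergence delirium". Type of surgery is listed under Intervention and Control, among the surgical and anesthesia data.

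Randomization and Blinding describes 1:1 allocation in blocks of 4 and names no stratification factor. The only adjusted model in the article is the Cox model for in-hospital mortality, under Secondary Outcome Analysis.

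**The concern.** The article names three factors as influencing the primary outcome and collects them, but neither the described randomization nor the primary test uses them. It states the aim of removing their influence and assigns that aim to subgroup analyses. A subgroup analysis asks whether the treatment effect differs between kinds of patient, using smaller samples. It leaves the overall comparison exactly as it was.

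Two things are at stake. First, some precision and power that could be had without recruiting anyone. Second, protection against a chance imbalance. Baseline Analyses plans significance tests of baseline characteristics. If one of them shows an imbalance in age or MoCA, the article names no adjusted primary result to turn to, and a model chosen at that point would be post hoc.

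**Working it through.** **Inputs from the article.** Control incidence 15%; reduction of 6%, read as absolute, so 9% on tropisetron; 640 evaluable per group (Sample Size Calculation). Two-sided tests at 0.05 (Secondary Outcome Analysis).

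**The plan's own figure.** With unpooled variance, n = (z_alpha + z_beta)² × [0.15×0.85 + 0.09×0.91] / 0.06².
- One-sided: (1.645 + 0.842)² × 0.2094 / 0.0036 = 360.
- Two-sided: (1.960 + 0.842)² × 0.2094 / 0.0036 = 457.

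Pooled variance gives 362 and 460. None of these is 640, so the stated size does not follow from its stated inputs. That is a separate point. The inflation step does hold: 640/0.85 = 753, against 754 stated. I take 640 per group as given, because it is the evaluable number the plan commits to.

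**Unadjusted precision at 640 per group.**
- SE = √(0.2094/640) = 0.01809.
- 95% CI half-width = 1.96 × 0.01809 = 3.55 percentage points.
- Power = Φ(0.06/0.01809 − 1.96) = Φ(1.357) = 91.3%.

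**Assumptions for adjustment.** The article gives no covariate effects or distributions. I assume 30% of patients over 65, 50% major surgery, and MoCA bands (>26, 18-26, 10-17) at 50%, 40% and 10%, all independent. Odds ratios, in the order age >65 / major surgery / MoCA 18-26 / MoCA 10-17, are:
- weak: 1.5 / 1.3 / 1.5 / 2
- moderate: 2 / 1.5 / 2 / 3
- strong: 3 / 2 / 3 / 6

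Marginal risks are held at 15% and 9%.

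**Variance of the standardized risk difference.** With p0 and p1 the cell-specific risks,

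n × Var = E[p0(1−p0)] + E[p1(1−p1)] + Var(p1−p0)/2.

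| Scenario | Sum of the three terms | Ratio to 0.2094 | Half-width (points) | Power, 15% vs 9% |
|---|---|---|---|---|
| Unadjusted | 0.2094 | 1 | 3.55 | 91.3% |
| Weak | 0.12558 + 0.08109 + 0.00012 = 0.2068 | 0.988 | 3.52 | 91.6% |
| Moderate | 0.12229 + 0.07964 + 0.00031 = 0.2022 | 0.966 | 3.48 | 92.2% |
| Strong | 0.11441 + 0.07586 + 0.00071 = 0.1910 | 0.912 | 3.39 | 93.5% |

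The variance falls by 1.2%, 3.4% and 8.8%. On 1280 evaluable patients, 1280 × (1/ratio − 1) is worth about 16, 45 and 124 additional patients.

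**A smaller effect, 15% versus 10%.** Unadjusted variance term 0.1275 + 0.0900 = 0.2175; power Φ(0.05/√(0.2175/640) − 1.96) = 77.4%. Adjusted power is 77.9%, 78.9% and 81.2%.

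**Check by simulation.** With 4000 trials per scenario at 15% versus 9%, chi-square against logistic regression with the three factors gave 91.0% and 91.0%, 92.3% and 92.9%, 91.7% and 93.8%.

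**Upper case.** A single continuous, correctly specified score with a log-odds slope of 1.2 per SD (AUC about 0.78) gave 91.5% unadjusted and 95.2% adjusted at 640 per group (4000 trials).

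**The case against.** The strongest reply is that nothing here is an error. A chi-square test with a CI for the difference is valid under 1:1 randomization, targets the stated outcome, and matches the two-proportion method used for sample size. The choice of an adjusted primary model is then a preference, and the gain at 640 per group is small because power for the planned effect is already about 91%. Supporting adjusted analyses may also sit in the full protocol or analysis plan, which are not shown.

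Most of this stands. The test is valid, the gain is modest, and the absence of supporting analyses is no finding. What remains is that the article itself fixes the primary test without covariates and gives the subgroups a job that they cannot do. Those are statements in the text, not details left out.

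Stronger readings are tempting, but the documents do not support them:
- **That the primary result will be confounded.** Randomization protects the comparison; only chance imbalance remains, and the test's error rate already allows for it.
- **That adjustment is worth 15% to 20% more patients.** This needs an AUC near 0.78, and no covariate effect or AUC appears in the article. The eligibility criteria also exclude neurological and psychiatric disease, MoCA below 10 and ASA status above III, which narrows the range of risk.
- **That the adjusted mortality model has too few events.** No mortality rate is given, so this cannot be judged.

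**Conclusion.** The point holds as a modest efficiency loss together with a wrongly stated purpose for the subgroups. It is not a validity error. At the planned 640 per group, adjusting for the three named factors would add about 0.3 to 2.2 power points at 15% versus 9%, and about 0.5 to 3.8 points at 15% versus 10%, where power is short of 80%. The CI half-width would shrink by 0.03 to 0.16 points. About 95% power with one very strong score is an upper case.

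Every figure for the gain rests on assumed odds ratios and case mix. The direction does not: prognostic baseline factors improve precision, and the article itself says that these factors matter. Since the gain costs no patients, visits or data, the change is worth making.

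**What to change.** Before unblinding:

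1. Make the primary analysis a logistic model with arm, age and MoCA as continuous terms, and planned surgery type (major or minor). Surgery type must be the classification made before randomization, because the article lists type of surgery among the perioperative data and only a pre-randomization value may enter the model.
2. Report the standardized (marginal) risk difference with its 95% CI, so that the quantity estimated stays the difference in incidence.
3. Keep the chi-square test and crude difference as the supporting analysis.
4. Reword Priori Subgroup Analyses, and the matching sentence in Strengths and Limitations, so that subgroups serve only to examine whether the effect differs between patients.

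The cost is small. The model must be fixed in advance, and standardization needs a few lines of code beyond the menus of SPSS, the package named for the analysis. The planned surgery class must also be available as a pre-randomization value.

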### Priori Subgroup Analyses

Known confounders have an impact on delirium; thus, subgroup analyses will be conducted by comparisons of prespecified subgroups for the primary outcome. These include age (>65 years vs ≤65 years), surgery type (major vs minor), and preoperative Montreal Cognitive Assessment scores (>26 vs 18-26 vs 10-17) to eliminate the impact of these factors on tropisetron efficacy.

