### Secondary Outcome Analysis

For secondary outcome analyses, the Mann-Whitney test will be used for length of hospital stay, whereas the χ^2^ test or the Fisher exact test will be used for categorical variables, including incidence of postoperative delirium within 3 days after surgery, nausea and vomiting, postoperative pain, and adverse events. For analysis of all-cause mortality during hospitalization, we will use Kaplan-Meier curves, with a log-rank test for between-group comparison. The Cox proportional hazards model will be used to estimate the hazard ratio among patients in the tropisetron group compared with the placebo group with adjusting for potential confounding factors.^42,43^

All statistical tests will be 2 sided, and statistical significance will be defined as *P* < .05. Statistical analysis will be performed with SPSS software, version 22.0 (SPSS, Inc).

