### Strengths and Limitations

There are several strengths of this study. The broad inclusion criteria of this study strengthens the external validity and clinical applicability. Predetermined subgroup analyses, such as age, surgery type, history of tobacco use, and other disturbances in cognitive function (anxiety, depression and insomnia) will mitigate these potential confounders, which could influence outcomes of our study.

This study has limitations that must be addressed. First, the trial is conducted at only 1 medical center, which restricts generalizability of the results. Second, symptoms of delirium fluctuate over time. Accurate identification of delirium at the assessing time may be difficult. We will perform delirium assessments at various times to ensure better detection.

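### Subgroup analyses are given the aim of removing confounding, which they cannot do in this randomized trial, and the two lists of prespecified subgroups name different factors

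*Protocol article*

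**What the plan says.** The section Priori Subgroup Analyses of the protocol article gives a reason and a method in one sentence: "Known confounders have an impact on delirium; thus, subgroup analyses will be conducted by comparisons of prespecified subgroups for the primary outcome". The factors are "age (>65 years vs ≤65 years), surgery type (major vs minor), and preoperative Montreal Cognitive Assessment scores (>26 vs 18-26 vs 10-17". The stated purpose is "to eliminate the impact of these factors on tropisetron efficacy".

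The section Strengths and Limitations returns to the subject: "Predetermined subgroup analyses, such as age, surgery type, history of tobacco use, and other disturbances in cognitive function (anxiety, depression and insomnia". It claims that these analyses "will mitigate these potential confounders, which could influence outcomes of our study".

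The overall comparison takes no account of these factors. Under Primary Outcome Analysis: "Comparisons in delirium incidence between the 2 groups will be assessed with a χ^2^ test", with a 95% CI for the difference. The significance rule at the end of Secondary Outcome Analysis is general: "All statistical tests will be 2 sided, and statistical significance will be defined as *P* < .05".

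**The concern.** Three different tasks are run together.

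- **Adjustment** asks for the overall effect with chance imbalance in a prognostic factor taken into account. It needs a stratified or covariate-adjusted estimate.
- **Heterogeneity** asks whether the effect differs between levels of a factor. It needs a test or interval for the difference between the stratum effects.
- **Subgroup description** shows the effect at each level.

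The plan states something close to the first aim and names a procedure that delivers only the third. An analyst who believes that splitting removes a factor's influence has no reason to run a test of heterogeneity, and may read each stratum's P value as a result in its own right. That habit produces reports that a drug works in the old but not the young when the effect is the same in both.

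The two lists add to this. If both are called fixed in advance but name different factors, a reader of the final report cannot tell which subgroups were planned.

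**Working it through.** **1. The two lists**

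| Factor | Priori Subgroup Analyses | Strengths and Limitations |
|---|---|---|
| Age | yes, cut at 65 | yes |
| Surgery type | yes, major/minor | yes |
| MoCA | yes, three bands | not named |
| Tobacco history | not named | yes, no cut-point |
| Anxiety, depression, insomnia | not named | yes, no cut-points |

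Four factors appear only in the second list and one only in the first.

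**2. What splitting does to the estimate**

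The overall estimate is d = x_P/n_P − x_T/n_T (events over patients, placebo minus tropisetron). No factor enters it. Splitting gives d_k in each stratum k and leaves d as it was. Evidence that the effect differs is carried by d_1 − d_2 and its standard error, not by comparing two P values. Because allocation is random, the factors differ between arms only by chance, so there is no systematic confounding to remove.

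**3. Inputs for the size of the risk**

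- From Sample Size Calculation: 15% in controls, 9% after a 6-point reduction, 640 per group before dropout.
- From Secondary Outcome Analysis: two-sided 0.05.
- Assumed, because the documents give none: the share of patients in each stratum. A range is shown.
- Also assumed: the same control rate and the same risk difference in every stratum.

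The plan's own figures: 640/0.85 = 753, against 754 stated, so the dropout step agrees to rounding. The 640 is not returned by the stated 80% power and one-sided 0.05; the usual normal approximation gives 362. That is a separate matter. I take 640 as the planned evaluable number.

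**4. Power within a stratum of n per arm**

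Power = Φ[(0.06√n − 1.96·s0)/s1], where s0 = √(2 × 0.12 × 0.88) = 0.4596 and s1 = √(0.15 × 0.85 + 0.09 × 0.91) = 0.4576.

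- n = 640: (1.518 − 0.901)/0.4576 = 1.349, power 91.1% (whole trial)
- n = 320: (1.073 − 0.901)/0.4576 = 0.377, power 64.7%
- n = 224 and 416: z = −0.006 and 0.706, power 49.8% and 76.0%
- n = 128 and 512: z = −0.485 and 0.998, power 31.4% and 84.1%

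**5. Chance that exactly one of two strata is significant, with a uniform effect**

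P1(1 − P2) + P2(1 − P1):

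- 50/50 split: 2 × 0.647 × 0.353 = 0.457
- 35/65 split: 0.498 × 0.240 + 0.760 × 0.502 = 0.501
- 20/80 split: 0.314 × 0.159 + 0.841 × 0.686 = 0.627

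For the three-level MoCA factor, the chance of significance in some but not all strata is about 75% (equal thirds) to 81% (50/40/10).

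**6. All three Methods factors together**

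Simulated with 640 per arm and factors independent of each other and of outcome. The result is the chance that at least one factor is significant in some strata but not all:

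| True rates | Result |
|---|---|
| 15% vs 9%, equal strata | about 85% |
| 15% vs 9%, strata 35/65, 50/50, 50/40/10 | about 90% to 91% |
| 15% vs 9%, age and surgery type only (35/65, 50/50) | about 64% to 65% |
| 15% vs 12%, three factors | about 56% to 57% |
| No effect, three factors, either direction | about 25% |
| No effect, three factors, favouring tropisetron only | about 12% to 13% |

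**7. With one interaction test per factor**

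Under a uniform effect the false signal rate is 5% per factor. Over three independent factors, uncorrected, it is 1 − 0.95³ = 14.3%.

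**The case against.** Several stronger readings are tempting, and the documents do not support them.

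- *The plan has no interaction test.* This is a condensed article that points to a full protocol in a supplement, and an analysis plan may exist. Such a test is commonly specified there, so its absence from the article is no finding. It enters here only as part of the remedy for a wrongly stated aim.
- *Efficacy will be claimed stratum by stratum.* The text says only that "subgroup analyses will be conducted by comparisons of prespecified subgroups for the primary outcome", which can be read as a comparison between subgroups. The percentages above are therefore conditional on significance being read within strata.
- *A spurious subgroup claim is likely.* That is so only under that reading and with an effect near the planned size. The three-factor figure also leans on the assumed MoCA shares and falls to about 64% to 65% without MoCA.
- *The Discussion drops MoCA and leaves the subgroups open to later choice.* That list is introduced as examples, so MoCA is not clearly dropped, and the Methods section does fix its own three factors in advance. What remains is that four factors called predetermined are absent from the Methods list.
- *The trial's main result is compromised.* It is not. The primary analysis is one overall test, and nothing in the subgroup sections feeds into it.

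These points narrow the concern. They do not touch the two sentences claiming that subgroup analysis deals with confounding. Further detail elsewhere would not make those sentences correct.

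**Conclusion.** The concern holds in this limited form: the stated purpose of the subgroup analyses is wrong in two places, and the two lists of factors need to be reconciled. Both faults lie in the text itself.

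The size of the exposure depends on how the subgroups are read, on the true effect and on the stratum shares. Within-stratum significance testing would show a one-stratum-only result in roughly half of trials for a single two-level factor when the planned effect is uniform, and in most trials across the three factors. The risk is smaller with a weaker effect. With no effect it is about a quarter, half of it in tropisetron's favour. The fault is worth correcting because it governs what the trial may say about subgroups; it gives no ground for doubting the primary comparison.

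**What to change.** Before unblinding:

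1. Settle one closed list of factors with cut-points, and make Priori Subgroup Analyses and Strengths and Limitations agree. The simplest choice is the Methods list: age, surgery type and MoCA.
2. Delete the claims that subgroup analyses eliminate or mitigate confounding. State the aim as assessing whether the effect of tropisetron differs across levels of each factor.
3. For each factor, fit a logistic model with arm, factor and arm-by-factor terms and report one interaction P value (2 degrees of freedom for MoCA). These factors are expected to change baseline risk, so the result can depend on the scale. As a check, add a homogeneity test of the stratum risk differences: Q = Σ w_k(d_k − d̄)², with w_k = 1/var(d_k), d̄ the w_k-weighted mean of the d_k, and (number of strata − 1) degrees of freedom.
4. Give the risk difference and 95% CI in each subgroup as descriptive, with no significance claim within a stratum.
5. If chance imbalance is the worry, add a covariate-adjusted analysis of the overall effect using age, surgery type and MoCA.

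Cost: a few sentences and a few extra models. The factors are already collected at baseline, and the sample size and primary test do not change.

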### Secondary Outcome Analysis

For secondary outcome analyses, the Mann-Whitney test will be used for length of hospital stay, whereas the χ^2^ test or the Fisher exact test will be used for categorical variables, including incidence of postoperative delirium within 3 days after surgery, nausea and vomiting, postoperative pain, and adverse events. For analysis of all-cause mortality during hospitalization, we will use Kaplan-Meier curves, with a log-rank test for between-group comparison. The Cox proportional hazards model will be used to estimate the hazard ratio among patients in the tropisetron group compared with the placebo group with adjusting for potential confounding factors.^42,43^

All statistical tests will be 2 sided, and statistical significance will be defined as *P* < .05. Statistical analysis will be performed with SPSS software, version 22.0 (SPSS, Inc).

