### Study Design and Setting

The study is being conducted in Beijing Chaoyang hospital affiliated with Capital Medical University, Beijing, China. The trial has been approved by the Medical Ethics Committee of the Chaoyang Hospital, Beijing. This study protocol is strictly in accordance with the Standard Protocol Items: Recommendations for Interventional Trials (SPIRIT) reporting guideline.^26,27^

The study is a double-blinded, randomized placebo-controlled trial that includes 1508 patients undergoing noncardiac surgery. Potential participants undergoing noncardiac surgery will be screened for eligibility criteria. All enrolled patients will be randomly divided into either the tropisetron group or placebo group at a 1:1 ratio. The primary end point is the incidence of emergence delirium.

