### Outcomes

The primary outcome in this study is the incidence of emergence delirium within 1 hour after tracheal extubation measured using the validated Chinese version of the CAM-ICU.^36^ The CAM-ICU was validated against the *Diagnostic and Statistical Manual of Mental Disorders* (Fifth Edition) criteria for delirium in PACU settings based on the guideline.^38^ With a specificity of 98% and low sensitivity, we may detect the positive delirium cases conservatively in this study.^39^ The positive CAM-ICU test result requires the presence of (1) acute changes in mental status with a fluctuating course and (2) inattention, with either (3) disorganized thinking or (4) altered level of consciousness. Patients with delirium may display hyperactive or hypoactive signs. Hyperactive delirium is defined as RASS scores from 1 to 4, and hypoactive delirium is defined as RASS scores from −3 to 0.^40^ Secondary outcomes include (1) incidence of postoperative delirium within 3 days after surgery (defined as positive CAM-ICU test result); (2) nausea and vomiting within 3 days after surgery; (3) postoperative pain intensity at PACU discharge and 24, 48, and 72 hours after surgery, measured using the visual analog scale (scores range from 0-10, with higher scores indicating greater pain); (4) adverse events (cardiac arrhythmias, cardiogenic shock, and other unexpected adverse events) within 3 days after surgery; (5) length of hospital stay; and (6) all-cause mortality during hospitalization.

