### Sample Size Calculation

The sample size calculation is based on the primary outcome. According to previous studies, the incidence of delirium diagnosed in the PACU ranged from 3.7% to 22.2%.^7,8,9^ We assumed an emergence delirium incidence of 15% in the control group and a 6% reduction (the clinical limit of superiority) in the intervention group. With a power of 80% and 1-sided α = .05 and using superiority tests for 2 proportions, 640 patients per group are required. With a dropout rate of 15%, the final planned total sample size is 754 randomized patients in each group. The sample size calculation was performed on PASS software, version 14.0 (Number Cruncher Statistical Software).

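### Postoperative pain is defined as a 0-10 intensity score but is assigned the chi-square or Fisher exact test for categorical variables, with no categories given

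*Protocol article*

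**What the plan says.** Two sections of the protocol article bear directly on this.

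- **Outcomes**, third secondary outcome: "postoperative pain intensity at PACU discharge and 24, 48, and 72 hours after surgery, measured using the visual analog scale". The scale is described in the same sentence: "scores range from 0-10, with higher scores indicating greater pain".
- **Secondary Outcome Analysis**: "the χ^2^ test or the Fisher exact test will be used for categorical variables", and the list of those variables reads "including incidence of postoperative delirium within 3 days after surgery, nausea and vomiting, postoperative pain, and adverse events". In the same sentence, "the Mann-Whitney test will be used for length of hospital stay".

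Three other places give context. **Baseline Analyses** assigns the t test or Mann-Whitney test to continuous variables and keeps chi-square and Fisher for categorical ones. **Priori Subgroup Analyses** bands one score, the Montreal Cognitive Assessment, and states its bands (above 26, 18-26, 10-17). **Baseline Hospital Ward Visit** records that, one day before surgery, "patients undergo assessments, including pain measured by a visual analog scale".

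**The concern.** The outcome is an ordered intensity score and the named test is for unordered categories. Nothing in the article turns the one into the other. The analysis can be read in two ways, and neither delivers the outcome as defined.

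1. *Chi-square or Fisher on the raw score levels.* The result is the same if the score labels are shuffled, so the test does not ask whether one group has more pain than the other. It also gives no estimate of how much more. If scores are recorded more finely than whole points, the table becomes sparser still.
2. *Chi-square or Fisher on a banded score.* The outcome is then a proportion above some threshold, not an intensity. The article gives neither the threshold nor the time or times at which it applies.

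What is at stake is the usefulness of one secondary result: a modest difference in pain could be missed, and a difference that is found would come without an effect size on the pain scale.

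**Working it through.** **Step 1. Is there a figure in the plan to reproduce?** No. The article gives no SD, target difference or power for pain. The mismatch itself is established by the text; arithmetic can only show what it may cost.

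**Step 2. Inputs.**

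| Input | Value | Source |
|---|---|---|
| Patients per group | 640 | Sample Size Calculation: "640 patients per group are required" |
| Allocation | 1:1 | Study Design and Setting |
| Significance level | 0.05, two-sided | Secondary Outcome Analysis |
| Scale | 0-10 | Outcomes |
| Integer scores, from a rounded and truncated normal | – | Assumption |
| Control mean | 3 (range 2 to 4) | Assumption |
| SD | 2 (also 1.5 and 2.5) | Assumption |
| Shift before rounding | 0.2 to 0.6 points | Assumption |
| Time points | one | Assumption |

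**Step 3. Simulated power, mean 3, SD 2.**

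| Shift (points) | Chi-square, all 11 levels | Chi-square, cut at 4 or more | Mann-Whitney |
|---|---|---|---|
| 0.2 | 16% | 28% | 41% |
| 0.3 | 37% | 56% | 73% |
| 0.4 | 66% | 82% | 94% |
| 0.6 | about 98% | about 98% | above 99% |

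With no shift, each test rejects in about 4-5% of trials.

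**Step 4. Hand check of the 0.3-point row.**

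- *Upper reference (t test).* z = 0.3 / (2 × √(2/640)) = 0.3 / 0.1118 = 2.68. Power = Φ(2.68 − 1.96) = Φ(0.72) ≈ 76%. Mann-Whitney at 73% lies just below.
- *Cut at 4 or more.* On the underlying scale, P(score ≥ 4) = P(Z > (3.5 − 3)/2) = P(Z > 0.25) = 0.401. With the mean shifted to 2.7 it is P(Z > 0.40) = 0.345. The difference is 0.401 − 0.345 = 0.057 (from unrounded values), and the pooled proportion is 0.373. The standard error is √(2 × 0.373 × 0.627 / 640) = 0.0270, so z = 0.0567 / 0.0270 = 2.10. Power = Φ(2.10 − 1.96) = Φ(0.14) ≈ 56%, as simulated.
- *All 11 levels.* The test spreads a one-directional shift over 11 − 1 = 10 degrees of freedom where an ordered test uses one. That is why its power falls to about half (37/73 = 0.51).

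**Step 5. Sensitivity to the assumptions** (same order of tests).

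- Mean 2 to 4, SD 2, shift 0.3: 37-39%, 47-58%, 71-75%.
- SD 2.5, shift 0.3, mean 3: 22%, 39%, 54%.
- SD 1.5, shift 0.4, mean 3: 94%, 95%, 99%.
- SD 2, shift 0.8, mean 3: at least 99.9% for all three.

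The order of the tests is stable where they differ. The size of the gap is not: it is wide for shifts near 0.3/2 = 0.15 SD and has almost closed at 0.6/2 = 0.30 SD.

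**Step 6. Baseline adjustment, for information.** Analysis of covariance reduces the SD by √(1 − r²). With an assumed correlation r = 0.3 the SD is 2 × √0.91 = 1.91, and power at 0.3 points is about 80%. With r = 0.5 it is 2 × √0.75 = 1.73, and power is about 87%. The article gives no value for r.

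**The case against.** **The power loss is conditional.** The article sets no target difference for pain and makes no power claim for it. The mean, SD and shifts above are assumed, and at larger shifts the loss all but disappears. This stands. The figures illustrate a range and are not facts about this trial.

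**Banded pain may have been meant.** Calling pain categorical can be read as a dichotomy, which keeps part of the order and costs less power. The cut-off could be in the full protocol, which the Trial Status section places in a supplement not shown here. This stands in part. It explains how a chi-square test could make sense, but the Outcomes section still defines an intensity score, and where the article bands another score it states the bands. A reader might infer that a cut-off would be picked after seeing the results; nothing in the article supports that.

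**The four times.** A reader might infer that the four correlated measurements will be run as separate tests. The Secondary Outcome Analysis section does not say how they are handled, so this would rest on silence alone.

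**The baseline score.** A reader might infer that leaving out the preoperative score is an error. It is not. An unadjusted comparison in a 1:1 randomized trial is valid, and the Baseline Hospital Ward Visit section says the preoperative assessments serve to identify risk factors for emergence delirium. Adjustment is an efficiency choice, and Mann-Whitney does not use the baseline score either.

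**Consequence.** Pain is one of six secondary outcomes and the listed test does not inflate false positives. Both points stand.

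**Conclusion.** The mismatch is in the text and does not depend on any assumption: the outcome is an ordered 0-10 score, the assigned test is for categorical variables, and the article defines no categories. This is not a detail left to a later plan, because the article itself names the test. The harm is a test that ignores order, the lack of an estimate of the difference in pain, and lower power against small shifts.

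How much power is lost rests on the assumptions listed: about half at a 0.3-point shift if all score levels are used, less with a cut at 4 or more, and almost none at 0.6 points. The finding does not extend to type I error or to the primary outcome, and it should be corrected as a matter of wording in a secondary analysis.

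**What to change.** 1. In Secondary Outcome Analysis, take postoperative pain out of the chi-square/Fisher list and add it to the Mann-Whitney sentence beside length of hospital stay. Report a between-group difference in score with 95% CI at each of the four times; the Hodges-Lehmann estimate pairs naturally with that test.
2. If a banded outcome was intended, state the cut-off and the time point before unblinding, and keep the score analysis alongside it.
3. Optional, for efficiency: a repeated-measures model over the four times with treatment, time, treatment by time and the Visit 1 visual analog score, reporting mean differences with 95% CIs.

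The cost is a change of wording. The scores, including the preoperative one, are already scheduled, the Mann-Whitney test is already in the plan, and no patients or visits are added.
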